### Four-month assessment of the control group

Four months after their baseline assessment, patients in the control group complete the Alcohol TLFB (covering the period from the baseline assessment to the present), the NHS resource utilisation questionnaire, the Drinking Urges Questionnaire, the Alcohol Stroop Test, the OCDS, and the POMS.

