**Methods/design:**

Participants are alcohol-dependent patients who have completed a detoxification programme within the past 6 months and have remained abstinent. Potential participants are screened for eligibility, and those who are eligible are randomly assigned to the treatment group (receiving rtfMRI NFT in addition to treatment as usual) or the control group (receiving only treatment as usual). Participants in both groups are administered baseline assessments to measure their alcohol consumption and severity of dependence and a variety of psychological and behavioural characteristics that are hypothesised to predict success with rtfMRI NFT. During the following 4 months, experimental participants are given six NFT sessions, and before and after each session various alcohol-related measures are taken. Participants in the control group are given the same measures to coincide with their timing in the experimental group. Eight and 12 months after the baseline assessment, both groups are followed up with a battery of measures. The primary research questions are whether NFT can be used to teach participants to down-regulate their brain activation in the presence of alcohol stimuli or to up-regulate their brain activation in response to pictures related to healthy goal pursuits, and, if so, whether this translates into reductions in alcohol consumption. The primary outcome measures will be those derived from the functional brain imaging data. We are interested in *improvements* (i.e., reductions) in participants’ alcohol consumption from pretreatment levels, as indicated by three continuous variables, not simply whether or not the person has remained abstinent. The indices of interest are *percentage of days abstinent*, *drinks per drinking day*, and *percentage of days of heavy drinking*. General linear models will be used to compare the NFT group and the control group on these measures.

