**Fig. 1 Fig1:**
[figure not shown]
Consolidated Standards of Reporting Trials (CONSORT) flow diagram of the phases of the BRAINTRAIN trial

**Table 1 Tab1:** Standard Protocol Items: Recommendations for Interventional Trials (SPIRIT) diagram

	Study period					
	Enrolment	Allocation				
Timepoint	Pre intervention	Time 0	Baseline	Post intervention	8-month follow-up	12-month follow-up
Enrolment:						
Eligibility screen	X					
Informed consent	X					
Allocation		X				
Interventions:						
rtfMRI NFT + TAU				X		
TAU				X		
Assessments:						
Alcohol Timeline Followback	X		X	X	X	X
Drinking Urges Questionnaire			X	X	X	X
Obsessive Compulsive Drinking Scale			X	X	X	X
Alcohol Stroop Test			X	X	X	X
Severity of Alcohol Dependence			X			
Thought Control Questionnaire			X			
Thought Control Ability Questionnaire			X			
Profile of Mood States			X		X	X
Hospital Anxiety and Depression Scale			X	X	X	X
Beck Depression Inventory			X	X	X	X

*rtfMRI* real-time functional magnetic resonance imaging, *TAU* treatment as usual

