### Assessment at NFT sessions

At each of the six NFT sessions across 4 months, patients in the experimental group complete the Drinking Urges Questionnaire (before and after the MRI scan), a self-rating of craving during the scanning session, the Alcohol TLFB (only after the last training session and covering the period from the baseline assessment to the present), the Alcohol Stroop Test (only after the last training session); the OCDS (only after the last training session); the HADS (only at the last training session); the BDI (only at the last training session); a debriefing interview questionnaire to identify strategies that participants used to down-regulate their brain reactions to alcohol stimuli (and up-regulate their brain responses to other goal-related pictures), their general experience with the procedure, and any adverse reactions that they might have experienced.

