### Follow-up assessments

Eight and 12 months after the baseline assessment, both the experimental group and the control group are administered the Alcohol TLFB (covering the period from the previous assessment to the present), the NHS resource utilisation questionnaire, the Drinking Urges Questionnaire, the Alcohol Stroop Test, the OCDS, the POMS, the HADS, and the BDI.

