While in the scanner, participants in the experimental group are again exposed to alcohol-related stimuli, such as pictures of alcoholic drinks, and they are trained to regulate their responses in specific brain regions that are activated by the stimuli. In addition, participants are exposed to pictures showing alternative, socially desirable goals, such as family/relationships or employment. The rationale for including the two categories of stimuli is that we earlier demonstrated at a neural level that heavy drinking is associated with overvaluation of alcohol and undervaluation of alternative, socially desirable goals [14]. Moreover, consistent with motivational theory [15–17], it has been shown that problem drinkers’ success in reducing their drinking is associated with the degree to which they have other satisfying alternative goals to pursue and enjoy [16].

The size of the images that participants see corresponds to the level of activation. They are told to use any kind of mental strategy at their disposal (e.g. thinking about the negative consequences of drinking) that helps to reduce size of the image (in the case of alcohol pictures) or increase size of the image and thereby the degree of brain activation (in the case of healthy, goal-related pictures).

Experimental participants have six NFT training sessions spread across 4 months, and they are also asked to practice at home the mental strategies they used in the MRI scanner. They also (1) rate their urges to drink before, during, and after each training session, and (2) complete questionnaires and other tests to measure their alcohol consumption and other relevant aspects of their behaviour. Control participants complete the same measures that are timed to coincide with their administration to the experimental group. The primary outcome measures are obtained 4 months after the baseline assessment. Eight and 12 months after baseline assessment both groups complete a follow-up assessment battery.

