The behavioural data will be analysed using SPSS or another appropriate statistical software package. The primary analyses will compare the experimental and control groups on three drinking indices (percentage of days abstinent, drinks per drinking day, and percentage of days of heavy drinking) at the primary endpoint (4 months after the baseline assessment). For these analyses, a general linear model will be used. Covariates will include potential variables that determine participants’ success with the NFT (e.g. their age and gender and drinking indices at baseline) and the variables that were used to balance the two groups during randomisation. Effect sizes for the intervention will be evaluated using confidence intervals around the group difference. Analyses will be conducted separately for the follow-up assessments, again using general linear models adjusted for baseline covariates and randomisation variables. Outcome measures related to craving will be evaluated for both immediate and sustained effects of the NFT.

In exploratory analyses, data from the homework diaries will be examined for a potential relationship between the amount of self-regulation practice that participants report and their scores on craving and alcohol consumption. Finally, the relationship between nonalcohol-related measures (e.g. thought control ability, intellectual ability) and the alcohol-related outcome measures will be examined using analysis of covariance (ANCOVA) or correlational and regression analyses. Nonspecific effects of the NFT on participants’ mood will be examined using the measures related to emotional processes (e.g. the POMS).

A publication policy will be developed and reviewed during the course of the trial, which will include details of dissemination plans to health care professionals. Publications from the BRAINTRAIN consortium will be coordinated by the Executive Committee of BRAINTRAIN (chaired by the PI) in collaboration with the funding organisation. The trial results will be submitted for publication in an online open access journal.

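### The four-month schedules give the two arms different mood scales, in conflict with Table 1 and the same-measures statement; followed as listed, they leave no between-arm mood comparison at the end of training

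*Protocol article*

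**What the plan says.** The protocol article describes the four-month measurements in four places.

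- **Assessment at NFT sessions.** For the experimental arm the mood instruments are "the HADS (only at the last training session); the BDI (only at the last training session". The POMS is not in this list.
- **Four-month assessment of the control group.** After the drinking calendar and the health-service questionnaire, the list runs "the Drinking Urges Questionnaire, the Alcohol Stroop Test, the OCDS, and the POMS". The HADS and BDI are not in it.
- **Table 1 (SPIRIT diagram).** The post-intervention column is not split by arm. The row "Hospital Anxiety and Depression Scale" is marked there, as is the BDI row. The row "Profile of Mood States" is marked only at baseline, 8 months and 12 months.
- **Intervention.** After describing the experimental arm's questionnaires on drinking and other behaviour, the text says: "Control participants complete the same measures that are timed to coincide with their administration to the experimental group". The Abstract has a similar sentence, "Participants in the control group are given the same measures to coincide with their timing in the experimental group", but it follows a reference to alcohol-related measures, so it is weaker evidence about mood scales.

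At 8 and 12 months a single list covers both arms and ends with "the OCDS, the POMS, the HADS, and the BDI". At baseline, Table 2 gives all three scales to everyone. On the use of these data, the Analyses section says that nonspecific effects on participants' "mood will be examined using the measures related to emotional processes (e.g. the POMS" being the one scale named. It states no time point.

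**The concern.** A between-arm difference at a visit can be estimated only for an instrument that both arms complete at that visit. Read literally, the two arm-specific lists share no mood scale at four months. That visit is the end of the training period and the primary endpoint for drinking, so it is where an effect of NFT on mood would most naturally be sought. The one scale the Analyses section names for this purpose, the POMS, would exist at that visit in the control arm only.

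If staff work from these lists, the first mood measurement after baseline common to both arms is at month 8, which is 8 − 4 = 4 months after training ends. Current mood cannot be collected in retrospect, and the Trial status section says recruitment is under way.

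**Working it through.** No sample size or power figure is involved. The check compares the instruments listed per arm at each time point.

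**Inputs.** NFT arm at the last session: section on assessment at NFT sessions. Controls at four months: section on the four-month assessment. Months 8 and 12: section on follow-up assessments. Table 1 is set against these. The last NFT session is taken as the NFT arm's four-month assessment, since the six sessions span four months and no separate four-month visit is described for that arm.

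| Instrument | NFT list, last session | Control list, 4 months | Table 1, post intervention | Follow-up list, 8 and 12 months (both arms) |
|---|---|---|---|---|
| Alcohol TLFB | yes | yes | yes | yes |
| Drinking Urges Questionnaire | yes | yes | yes | yes |
| Alcohol Stroop Test | yes | yes | yes | yes |
| OCDS | yes | yes | yes | yes |
| POMS | no | yes | no | yes |
| HADS | yes | no | yes | yes |
| BDI | yes | no | yes | yes |

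**Mood scales common to both arms**, out of POMS, HADS and BDI:

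- Four months, by the two arm-specific lists: {HADS, BDI} ∩ {POMS} = none, so 0 of 3.
- Four months, by Table 1 read with the same-measures statement: HADS and BDI, so 2 of 3.
- Months 8 and 12: 3 of 3. Baseline (Table 2): 3 of 3.

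**Other outcomes at four months.** The instruments common to both arm-specific lists are the TLFB, the Drinking Urges Questionnaire, the Stroop test and the OCDS. The three drinking indices compared at the primary endpoint concern alcohol consumption, which the TLFB records, and both arms complete it.

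**Where the conflict sits.** The NFT list agrees with Table 1 on all three mood scales. The control list departs from Table 1 on all three: it adds the POMS and drops the HADS and BDI. Table 1, the NFT list and the Intervention section can therefore all hold together (HADS and BDI in both arms), and the control list is the outlier. No reading satisfies all four places.

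**The case against.** The strongest reply is that this is a drafting slip in one sentence of a condensed article. Three of the four places agree with one another. The article also refers to a study protocol and Case Report Forms that are not shown, so what is actually administered is unknown. This stands as far as it goes: the documents do not show that the trial was deliberately built without a common mood scale. It does not remove the point, because the article gives explicit arm-specific lists that contradict its own table. Nor would aligning the control list with Table 1 supply the POMS in the NFT arm at four months.

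A reader might also infer three stronger things, none of which the documents support.

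- **That the planned mood comparison cannot be made at all.** The Analyses section ties it to no visit and names the POMS only as an example. Both arms have all three scales at baseline, 8 and 12 months.
- **That the primary comparison is compromised.** It rests on drinking indices, and both arms complete the TLFB. Table 2 labels the mood scales as BRAINTRAIN core measures, not as primary or secondary outcomes.
- **That the site fails to supply a promised four-month mood contrast to the cross-trial work.** The section on core outcome measures promises none at any stated time.

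It can also be said that adding the POMS for the NFT arm goes beyond resolving the contradiction. That is fair: Table 1 does not schedule it at that visit. It is recommended because the Analyses section names the scale and the control list already includes it.

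**Conclusion.** The point holds as an internal contradiction with a bounded consequence. The four places that describe the four-month measurements cannot all be followed. If the two arm-specific lists are the ones used, no between-arm mood contrast can be estimated at the end of training, on any of the three scales, for any of the 25 + 25 planned participants. If Table 1 and the same-measures statement are used instead, two of the three scales are comparable and the POMS is not. The loss is at most one time point of a non-primary analysis. It is still worth correcting now, because it cannot be repaired after the visit has passed.

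This rests on two assumptions: that the arm-specific lists are meant to be complete for mood instruments, and that Table 1's post-intervention column is the four-month assessment in both arms.

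**What to change.** Establish from the Case Report Forms which mood scales each arm is actually completing at four months. Then reconcile the NFT session list, the control four-month list, Table 1 and the same-measures sentence in the Intervention section.

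- **At minimum:** add the HADS and BDI to the control group's four-month list, in line with Table 1. This gives 2 of 3 scales in common.
- **Preferably also:** add the POMS for the NFT arm at the last session and mark it in Table 1's post-intervention column. This gives 3 of 3, as at 8 and 12 months, and covers the scale the Analyses section names.

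The cost is one short questionnaire per NFT participant and two per control, at visits that already take place. At full enrolment that is at most 25 × 1 + 25 × 2 = 75 extra questionnaire completions, and fewer if some are already being given. If some participants have already passed four months under differing lists, the report should state how many have each scale in each arm at that visit.

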A moving average filtre of four volumes is used to overcome spikes and signal drops and to avoid large fluctuations in the size of the pictures. The percentage signal change is calculated using this equation:$$ fb = \left( val-bl\right)/bl\ast 100 $$

The percentage signal change (PSC) is then normalised to a value between −1 and +1 by dividing the *fb* value by a predefined maximum PSC of 1 %. This is done in order to be able to resize the pictures in the predefined way.

Between the *f*MRI runs, the experimenter speaks to the participant using an intercom and gives the participant the opportunity to rest. Participants in the control group are invited to attend four behavioural assessment sessions (baseline assessment, primary assessment after 4 months, and a follow-up assessment after 8 and 12 months).

All adverse events and serious adverse events (SAEs) will be recorded on the appropriate Case Report Form. Events meeting the criteria for a SAE will be reported according to the timelines specified in the study protocol (e.g. an SAE form should be completed for all SAEs within 24 h).

Post trial, all participants will remain under the care of their primary treating physician. Cardiff University will provide indemnity and compensation in the event of a claim by a participant, or by someone on a participant’s behalf, for negligent harm as a result of the study design and/or in respect of the protocol authors/research team. Cardiff University does not provide compensation for non-negligent harm.

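### The 4-month mood scales conflict between the two arm-specific lists and Table 1, and session-level urge ratings exist only in the NFT arm, despite statements that controls receive the same measures

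*Protocol article*

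**What the plan says.** Two places promise matched assessment. The abstract (Methods/design) states: "Participants in the control group are given the same measures to coincide with their timing in the experimental group". The Intervention section states: "Control participants complete the same measures that are timed to coincide with their administration to the experimental group". The sentence just before that one says that NFT participants "rate their urges to drink before, during, and after each training session".

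The detailed lists differ by arm:

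- **NFT arm** (Assessment at NFT sessions): the list includes "the HADS (only at the last training session); the BDI (only at the last training session"). The POMS does not appear.
- **Control arm** (Four-month assessment of the control group): after the Timeline Followback (TLFB), the NHS resource questionnaire and the Drinking Urges Questionnaire, the list closes with "the Alcohol Stroop Test, the OCDS, and the POMS". HADS and BDI do not appear.
- **Table 1**: a single post-intervention column covers both arms. It marks the row "Hospital Anxiety and Depression Scale" and the BDI row, and leaves POMS blank.

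On visits, the Intervention section says "Participants in the control group are invited to attend four behavioural assessment sessions", and gives these as baseline, 4, 8 and 12 months. Follow-up assessments lists POMS, HADS and BDI for both arms at 8 and 12 months.

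The Analyses section says: "Outcome measures related to craving will be evaluated for both immediate and sustained effects of the NFT". It also plans to examine non-specific mood effects, naming the POMS as an example and giving no time point. The 4-month primary endpoint is attached there to the three drinking indices.

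**The concern.** A reader who relies on the abstract or the Intervention section will assume that every measure taken in the NFT arm has a control value at the same time. The instrument lists do not deliver that for mood at 4 months or for urges at the training sessions.

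Two things are at stake. First, the section on core outcome measures says that the depression and anxiety scales are there to examine non-specific effects of NFT and to add power across the BRAINTRAIN trials. If sites follow the arm-specific lists, that comparison has no 4-month data in this trial. Second, urges belong to a main aim: Study objectives asks whether training reduces them relative to controls. A change from before to after a scan, seen in one arm only, mixes NFT with cue exposure, being scanned and the passage of time. Such a change cannot by itself answer a question framed against controls.

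Trial status says recruitment is under way, so 4-month values not collected in one arm cannot be recovered later.

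**Working it through.** The plan gives no figure on this point, so the check is a comparison of lists. The last NFT session is taken as that arm's 4-month assessment.

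**Step 1. Mood scales by source**

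| Scale | Baseline, both arms (Tables 1 and 2) | 4 months, NFT list | 4 months, control list | Table 1, post intervention (arms not separated) | 8 and 12 months, both arms |
|---|---|---|---|---|---|
| HADS | yes | yes | no | yes | yes |
| BDI | yes | yes | no | yes | yes |
| POMS | yes | no | yes | no | yes |

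**Step 2. Scales common to both arms at 4 months**

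- Arm-specific lists: {HADS, BDI} ∩ {POMS} = none, so 0 of 3.
- Table 1, read as applying to both arms: {HADS, BDI}, so 2 of 3.
- At 8 and 12 months: 3 of 3.

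Table 1 agrees with the NFT list and disagrees with the control list on all three scales. The POMS, the one scale that Analyses names as an example for mood, is listed for the NFT arm at 4 months neither in its own section nor in Table 1. Only the general statements about matched measures would put it there.

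**Step 3. Other 4-month instruments**

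Common to both arm-specific lists: TLFB, Drinking Urges Questionnaire, Alcohol Stroop Test and OCDS. The NHS resource questionnaire is listed for controls only.

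**Step 4. Urge ratings after baseline and up to 4 months**

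- NFT arm: 6 sessions × 2 Drinking Urges Questionnaires (before and after the scan) = 12, plus a craving self-rating during each session.
- Control arm: one visit after baseline in this period, at 4 months, so 1 Drinking Urges Questionnaire.

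The six within-session changes therefore have no control counterpart.

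**Step 5. Craving between arms**

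The Drinking Urges Questionnaire and the OCDS are listed for both arms at 4 months (the two arm-specific sections) and at 8 and 12 months (Follow-up assessments). Between-arm comparison of craving is available at all three times.

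**The case against.** The strongest reply is that the lists contradict each other rather than settle the matter. Table 1 gives a reading in which HADS and BDI are common at 4 months, and the control list may simply be the outlier. That stands: a reader might infer that the trial definitely has no common mood scale at 4 months, but the article does not say which source governs. What can be said is that the three sources must be reconciled.

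A reader might also infer that mood and craving effects cannot be compared between groups at all. The article does not support this. All three mood scales are taken in both arms at baseline, 8 and 12 months, and Analyses ties the mood analysis to no time point. Craving has common instruments at 4 months. The term immediate is not defined in Analyses. It could mean the end of training as opposed to later follow-up, and on that reading a comparator exists. Even if it means before and after a scan, the section does not call it a between-group contrast. Analyses also gives session craving scores a within-arm use, correlation with self-regulation. An arm that is not scanned has no natural counterpart to such a rating.

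The 4-month NHS resource questionnaire is listed for controls only, but Analyses describes no analysis of it, so no consequence can be shown.

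Finally, mood scales are core measures for non-specific effects, the craving instruments are secondary in Table 2, and the drinking indices come from the TLFB, which both arms complete at 4 months. That limits the weight of the point. It does not remove the contradiction with the two statements on matching.

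**Conclusion.** The point holds as an internal contradiction at the primary time point. The NFT list, the control list and Table 1 cannot all be followed, and neither the abstract nor the Intervention section is right that measures and timing match. If the arm-specific lists are followed, 0 of 3 mood scales are common at 4 months, and between-arm mood comparison after baseline is confined to 8 and 12 months. If Table 1 governs, 2 of 3 are common and only the POMS is lost at 4 months. Separately, the urge changes at all six sessions are uncontrolled, while craving at 4, 8 and 12 months can be compared between arms.

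This rests on taking the last NFT session as the 4-month assessment and on reading the lists as complete. No bias or loss of power in the primary drinking indices follows. The correction is worth making while patients are still being recruited, but it does not put the primary analysis in doubt.

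**What to change.** 1. Reconcile Table 1, Assessment at NFT sessions and Four-month assessment of the control group, so that both arms complete the same mood scales at 4 months. That means at least HADS and BDI, as in Table 1, and POMS in both arms if it is to be analysed at that time.
2. Correct the statements in the abstract and the Intervention section so that they claim matching only for the assessments both arms attend.
3. State that within-session urge change is measured in the NFT arm only and is uncontrolled. Base between-arm conclusions on craving on the 4-, 8- and 12-month assessments, and say in Analyses what immediate refers to.

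Sending controls urge questionnaires remotely at six matched times is not recommended as a cure. It would address the passage of time but leave cue exposure and scanning confounded with NFT.

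The cost is a few questionnaires at a visit that already exists, plus edits to one table and a few sentences. Any 4-month mood data already missed in one arm would remain missing.
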